##### Consideration for recurrence prediction validation

In this study, we aim to validate a machine-learning-based lung cancer recurrence prediction model with anticipated sensitivity of 90% ± 10% and specificity of 90% ± 10%. To calculate the necessary sample size for this diagnostic validation, we anchor our calculations to a fixed two-year recurrence (event) rate of 20%, based on retrospective study of recurrence after complete resection of early NSCLC.^[17, 18]^

Using Buderer’s formula for sensitivity and specificity sample size estimation:^[19, 20]^

$$N=\frac{Z^{2}\cdot p(1-p)}{d^{2}\cdot \text{ Prevalence }}=\frac{(1.96{)}^{2}\cdot 0.9\cdot 0.1}{0.1^{2}\cdot 0.2}\approx 173\text{ patients }$$

Here p is the anticipated sensitivity or specificity (0.90), d is the half-width of the 95% confidence interval (0.1), and Prevalence is the event prevalence (0.25). This calculation yields approximately 173 patients required to estimate sensitivity and specificity with ±10% precision at α = 0.05.

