##### Consideration for machine learning modeling

The novel lung cancer recurrence prediction model will be constructed based on machine-learning algorithms (section 5.2). For the model development, we adopt a ratio of 6:2:2 for the training, validation, and test sets. This division ratio is based on the consideration that 60% training provides adequate data for model fitting and feature selection, while 20% validation allows unbiased hyperparameter tuning, and 20% test ensures a fully held-out assessment to guard against overfitting. This ratio balances model complexity and evaluation rigor, as recommended for medium-sized cohorts.^[21, 22, 23]^ When 173 patients are recruited for statistical power in the training set, a total of 289 cases are required.

In summary, to address the above three dimensions of statistical consideration and the disruption caused by loss to follow-up, we plan to enroll 300 patients in the first phase. This provides sufficient power for survival analysis while also accommodating downstream modeling requirements.

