### Machine learning model development and validation

The patients recruited in the first phase of this study will be randomly divided into training set, test set and validation set according to the ratio of 6: 2: 2. Considering the “events per variable” (EPV) rule, we apply the following steps to develop a robust recurrence prediction model. First, we will not treat all molecular features as separate predictors. Instead, we will compute summary metrics to reduce dimensionality (see section 5.1). Then Least Absolute Shrinkage and Selection Operator (LASSO) regression will be applied within the training subset to identify the most informative predictors, where the penalty parameter will be selected *via* grid search in nested 5-fold cross-validation. This procedure typically yields less than 9 variables, satisfying EPV≥10 given an expected 80 events (26.7% of the 300 patients).

All parameter tuning will be confined to the training set to avoid information leakage. Machine learning-based classifiers will be implemented on the training set with 1000 rounds of ten-fold cross validation. In each round, the training set will be split into 10 subsets (folds); in each fold, a model will be trained on nine of the subsets and then validated on the remaining subset to tune the hyperparameters. Then we will apply all obtained models to the test set and compare the performance measurements. The optimal method will be used to construct the final model. The tested algorithms included: adaptive boosting (AdaBoost), decision tree, logistic regression, linear support vector machine (Linear SVM), radial basis function kernel support vector machine (RBF SVM), naive Bayes, nearest neighbors, neural net, quadratic discriminant analysis (QDA), random forest, and extreme gradient boosting (XGBoost). All machine learning algorithms have a solid research foundation.^[35]^

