#### Missing data handling

Clinical and laboratory data will be monitored for completeness. Missing data will be addressed *via* multiple imputation using chained equations (MICE), incorporating baseline covariates, clinical outcomes, and molecular features. We have defined a maximum acceptable loss-to-follow-up rate of 10%. If the actual loss rate exceeds 10%, we will compare baseline characteristics of completers and non-completers to assess potential bias. Sensitivity analyses by comparing complete-case and imputed datasets will be reported to demonstrate the impact of missingness on key study findings.

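### The recurrence model is sized on inconsistent event rates, and at the 20% rate behind 173 and 289 the total of 300 absorbs only 3.7% loss and gives EPV 7.5, not 10

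*Protocol article*

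**What the plan says.** All references are to the protocol article.

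- **Consideration for recurrence prediction validation.** The text says "we anchor our calculations to a fixed two-year recurrence (event) rate of 20" per cent, and the formula substitutes 0.2 to reach 173 patients. The line explaining the symbols then says "Prevalence is the event prevalence (0.25").
- **Consideration for machine learning modeling.** The 173 is assigned to the 60% training share: "When 173 patients are recruited for statistical power in the training set, a total of 289 cases are required". The total is then raised to 300: "to address the above three dimensions of statistical consideration and the disruption caused by loss to follow-up, we plan to enroll 300 patients". No loss rate is given there.
- **Missing data handling.** "We have defined a maximum acceptable loss-to-follow-up rate of 10" per cent. Above that limit, completers and non-completers are to be compared.
- **Machine learning model development and validation.** LASSO selection within the training subset is expected to leave fewer than nine predictors. EPV of at least 10 is claimed "given an expected 80 events (26.7% of the 300 patients").

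**The concern.** One model, with one outcome, should be planned on one event rate. Here the rate is 20% in the text and formula, 25% in the definition of the same symbol, and 26.7% in the EPV argument. The lower rate drives the sample size and the higher one supports the EPV claim, and no reason is given for the change. Someone who works from the definition cannot reproduce the 173 on which 289 and 300 depend.

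The statement that 300 takes care of losses rests on a margin of 11 patients. Losses between 3.7% and 10% would be acceptable under the article's own limit and would trigger no check, yet would leave fewer than the 289 it says are required. At stake are the stated precision of sensitivity and the assurance that the number of predictors suits the number of events.

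**Working it through.** **Inputs.** Anticipated sensitivity 0.90, half-width 0.10, Z = 1.96 and recurrence rate 0.20, with 0.25 in the definition (Consideration for recurrence prediction validation). Training share 0.6, required total 289, enrolment 300 (Consideration for machine learning modeling). Loss limit 10% (Missing data handling). At most 8 predictors, 80 events, 26.7% (Machine learning model development and validation).

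**1. The plan's own figures.** N = 1.96² × 0.9 × 0.1 / (0.1² × prevalence) = 34.5744 / prevalence.
- At 0.20: 172.9, so 173. This reproduces.
- 173 / 0.6 = 288.3, so 289. This reproduces.
- 80 / 300 = 26.7% and 80 / 8 = 10. The EPV claim is therefore met exactly, with nothing to spare, at eight predictors.

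**2. Room for losses at 20%.**
- (300 − 289) / 300 = 11 / 300 = 3.7%.
- 289 evaluable after 10% loss would need 289 / 0.9 = 321.1, so 322 enrolled.
- 300 × 0.9 = 270 evaluable; 270 × 0.6 = 162 in training, against 173.
- 162 × 0.20 = 32.4 recurrences; half-width = 1.96 × √(0.09 / 32.4) = 0.103.

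**3. The same chain at each stated rate.**

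| Rate | Buderer N | Total (N / 0.6) | With 10% loss | Compared with 300 |
|---|---|---|---|---|
| 20% | 173 | 289 | 322 | short |
| 25% | 139 | 232 | 258 | enough |
| 26.7% | 130 | 217 | 242 | enough |

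**4. EPV with eight predictors, counting events in the whole cohort as the plan does.**

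| Rate | Events in 300 | EPV | Events in 270 | EPV |
|---|---|---|---|---|
| 20% | 60 | 7.5 | 54 | 6.8 |
| 25% | 75 | 9.4 | 67.5 | 8.4 |
| 26.7% | 80 | 10.0 | 72 | 9.0 |

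**5. EPV where the predictors are actually selected.** The training set is 300 × 0.6 = 180.
- At 20%: 36 events, EPV 36 / 8 = 4.5. After 10% loss: about 32 events in 162, EPV about 4.
- At 26.7%: 48 events, EPV 48 / 8 = 6.0.

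**The case against.** Several points can fairly be made for the plan, and most of them limit the finding.

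- **The 0.25 enters no calculation.** The sentence before the formula says 20%, the formula uses 0.2, and 173 follows only from 0.2. A reader might infer that 173 is miscalculated. It is not; the definition is wrong, and the 139 only shows that it cannot be what was meant.
- **The 10% is a tolerance, not a planning rate.** It triggers a comparison of completers with non-completers, and the article nowhere says that 300 was inflated for 10%. So it would go too far to say that a stated 10% inflation was done wrongly. What stands is that losses are said to be dealt with, no other rate is given, and the margin is about a third of what the article accepts.
- **Multiple imputation is planned and includes clinical outcomes.** Treating every lost patient as removed is therefore my assumption. Imputed outcomes would not, however, add observed recurrences.
- **The effect on precision is small.** A half-width of 0.103 instead of 0.100 would change no decision.
- **A higher rate removes the shortfall.** A reader might infer that no single event rate satisfies all the requirements. That is not so: at 26.7% with no loss, 300 exceeds the stated 172 for the survival comparison (taken as given here) and the 217 for the model, and EPV is 10 on the plan's whole-cohort count. Even after 10% loss, 72 events support seven predictors (72 / 7 = 10.3).
- **The 25% under Consideration for survival analysis is a different quantity.** It is a rate of recurrence or death, so it need not equal the recurrence rate and is no contradiction.

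The general range of 15% to 30% under Sample size calculation contains all three rates, but it does not reconcile two values for one symbol, nor 26.7% with a rate that the article calls fixed.

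**Conclusion.** The point holds in a limited form. The recurrence model is planned on inconsistent rates: 20% for the sample size, a mistaken 0.25 in the definition, and 26.7% for EPV. At the article's fixed 20%, two statements fail. EPV of at least 10 with eight predictors becomes 7.5 (6.8 after 10% loss), and 300 covers 3.7% loss rather than the 10% the article is prepared to accept.

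The EPV statement is the more serious of the two, because it falls well short of its target, while the loss of precision is slight. It is weaker still when events are counted in the training set: 4.5 at 20% and 6.0 at 26.7%.

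The loss shortfall depends on the 20% rate and disappears for the precision requirement at 25% or 26.7%. The two defects therefore cannot be settled separately. The calculations assume that lost patients contribute no outcome, that losses fall evenly across the split, and that 173 in training is the target, as the article states.

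**What to change.** 1. Under Consideration for recurrence prediction validation, correct the definition of prevalence to 0.20, the value in the formula.
2. Choose one two-year recurrence rate and use it there, under Consideration for machine learning modeling, and under Machine learning model development and validation. The separate rate of recurrence or death for the survival comparison may stay if it is labelled as such.
3. If the rate is 20%, replace the 80 expected events by 60 (54 after 10% loss), and give the training-set count, which is the relevant one: 36 of 180, or about 32 of 162 after loss.
4. Then lower the limit on predictors or withdraw the claim of EPV of at least 10. On the training-set count, 36 / 10 = 3.6 and 32.4 / 10 = 3.2, so either count supports three predictors.
5. Replace the statement that 300 deals with losses by the precision expected from 270 evaluable patients: 162 in training, half-width about ±10.3% at 20%.

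The cost is recalculation and wording, a slightly worse stated precision, and a clearly less favourable EPV statement. Enrolment does not change.

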#### Inclusion and exclusion criteria

##### Inclusion Criteria

(1) Age ≥ 18 years old; (2) Stage I-IIIA operable NSCLC (ninth AJCC); (3) Sufficient tumor tissue and blood sample with a suspected tumor with a short diameter of at least 15 mm on the preoperative image; (4) NSCLC was confirmed by histopathology, and clinical, imaging and follow-up data were available; (5) Eastern Cooperative Oncology Group (ECOG) Performance Status of 0–1; (6) Written informed consent.

#### Exclusion Criteria

(1) Any other current malignancy or malignancy diagnosed or relapsed within the last 5 years; (2) Evidence of distant metastasis before surgery or inoperable state; (3) Infectious diseases such as HIV, hepatitis B, hepatitis C or syphilis; (4) Insufficient tumor tissue or blood sample; (5) Clinical-pathologic data, imaging data, or follow-up data are not available.

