### Sample collection

#### Tissue samples

In order to accurately sample and record the position, we have developed a standardized multi-region sampling process. Initially, the surgical sample is dissected along its maximum diameter. Equal-sized samples are then taken from one side of the tumor using a skin perforator. For smaller tumors, consider sampling from various locations on the opposite side. Samples from at least two tumor regions must be separated by 0.3 cm to 1 cm, depending on the tumor size, for inclusion in the study. Border samples should be collected at the interface between tumor and normal tissue to ensure that both tumor and normal samples are obtained. Paired normal tissue samples should be taken at least 2 cm away from the tumor edge. Last but not least, the central coordinates of each sampling point were recorded using a double-scale square and documented with photographs.

All tissue samples must be immediately placed into freezing tubes for preservation at -80°C. If the tumor is sufficiently large, a set of paraffin-embedded samples should also be collected for all tissues.

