The advent of immune checkpoint inhibitors (ICIs) has revolutionized the perioperative integrated treatment of NSCLCs patients, ushering in a new era.^[38, 39]^ Clinical studies have demonstrated that neoadjuvant immunotherapy enables approximately 30% of NSCLC patients to achieve major pathologic response (MPR) or even a pathological complete response (pCR).^[40, 41]^ Despite these encouraging results, a significant number of patients do not benefit from neoadjuvant immunotherapy. Understanding the response mechanisms of neoadjuvant therapy is crucial for enhancing its therapeutic efficacy in resectable NSCLCs. However, no studies have yet explored the response mechanism of neoadjuvant immune efficacy from the perspective of tumor heterogeneity and evolution. In this study, we will uncover distinct immune characteristics and spatial structures during the neoadjuvant immune response.

MRD has proven to be a significant predictor of prognosis and therapeutic efficacy in lung cancer. Our previous research demonstrated that the tumor-node-metastasis-blood (TNMB) classification system provides superior prognostic predictive power compared to the traditional TNM staging, particularly when deciding on adjuvant therapy.^[42]^ This advancement is enabled by a patient-specific Prognostic and Potential Therapeutic Marker Tracking (PROPHET) approach, which monitors plasma ctDNA-MRD derived from tumor cells.^[43]^ Furthermore, the CLEVER study has shown that multi-region sampling yields more comprehensive somatic mutation information than single-region sampling. By tracking mutations in a personalized MRD panel from baseline tumor samples, we can assess evolutionary significance and clonality, aiding in therapeutic decision-making. For patients undergoing neoadjuvant therapy, the clinical utility of ctDNA in evaluating treatment efficacy and assessing prognosis will be further explored through dynamic ctDNA changes.

The findings from this study could significantly contribute to the development of personalized treatment strategies for lung cancer patients. The CLEVER study lays the groundwork for a deeper understanding of the pathogenesis, progression, and evolutionary patterns of lung cancer. This enhanced understanding may lead to improvements in screening, diagnosis, treatment, and prevention strategies for lung cancer.

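### Inclusion depends on follow-up and tumour tissue known only after consent, which contradicts the protocol's own loss-to-follow-up plan and can under-represent strong neoadjuvant responders

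*Protocol article*

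**What the plan says.** **Timing.** Under Patient management, written consent is obtained after the tumour board has chosen between upfront surgery and neoadjuvant therapy. Under Blood samples, neoadjuvant patients also give blood on day one of each course. They are therefore in the study before response, resection, tissue yield or follow-up is known.

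**Follow-up as eligibility.** Inclusion item 4 reads "NSCLC was confirmed by histopathology, and clinical, imaging and follow-up data were available". Exclusion items 4 and 5 read "4) Insufficient tumor tissue or blood sample; (5) Clinical-pathologic data, imaging data, or follow-up data are not available".

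**Tissue as eligibility.** Inclusion item 3 asks for "Sufficient tumor tissue and blood sample with a suspected tumor with a short diameter of at least 15 mm on the preoperative image". It does not say whether that image precedes or follows neoadjuvant therapy. Under Tissue samples, "Samples from at least two tumor regions must be separated by 0.3 cm to 1 cm", and the sentence goes on to make this a condition for being included in the study, not merely in the tissue analyses.

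**Loss to follow-up elsewhere.** The sample-size section counts loss within the 300 patients to be enrolled. Missing data handling sets a 10% maximum loss, plans multiple imputation with a complete-case comparison, and adds: "If the actual loss rate exceeds 10%, we will compare baseline characteristics of completers and non-completers to assess potential bias".

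**Use of the cohort.** Two-year DFS and OS are the primary endpoints and predictors of clinical benefit are secondary. Confounding bias correction compares the neoadjuvant and naïve cohorts by matching and regression on age, sex, smoking, clinical stage and ECOG status.

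**The concern.** In a prospective cohort, whether follow-up is available is settled only during the two years in which the endpoints accrue. If it is also an entry criterion, a lost patient is reclassified as never eligible. The denominator then contains only patients who were followed. Any link between loss and outcome is hidden, and the 10% check has nothing to count.

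The tissue rule has a different effect. In the naïve cohort it mainly reflects tumour size and specimen handling. In the neoadjuvant cohort it also reflects how well treatment worked, because a patient with no residual tumour may not yield two tumour regions. Selection on a consequence of treatment, in one cohort only, affects the neoadjuvant versus naïve comparison. It also narrows the range of response in which the study hopes to find response markers.

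**Working it through.** **1. The passages side by side.**

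| Question | Eligibility and Tissue samples | Sample size and Missing data handling |
|---|---|---|
| Is a patient lost to follow-up a cohort member? | No, as worded | Yes: counted in the 300, compared with completers, imputed |
| When can the rule be judged? | After surgery, and during follow-up | Not applicable |
| Is two-region tissue needed for the study or for an analysis? | For inclusion in the study | Not addressed |

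Both answers to the first question cannot hold.

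**2. The plan's own enrolment figures.** 1.96² × 0.9 × 0.1 / (0.1² × 0.2) = 172.9, so 173, which reproduces. 173 / 0.6 = 288.3, so 289, which reproduces. Enrolling 300 leaves 11 patients, or 11/300 = 3.7%, for loss. This confirms that the plan expects lost patients to be among the 300. The point does not otherwise rest on these figures.

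**3. Removing lost patients.** From the document: two-year DFS event rate p = 25% and loss L = 10%. Assumed: r, the event rate in lost patients relative to retained ones. The rate seen in retained patients is p / [(1 − L) + L·r].

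| r (assumed) | Calculation | Observed rate | Shift (points) |
|---|---|---|---|
| 0.5 | 0.25/0.95 | 26.3% | +1.3 |
| 1 | 0.25/1.00 | 25.0% | 0 |
| 1.5 | 0.25/1.05 | 23.8% | −1.2 |
| 2 | 0.25/1.10 | 22.7% | −2.3 |
| 3 | 0.25/1.20 | 20.8% | −4.2 |

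The shift is zero only if loss is unrelated to outcome. Without assuming r: if retained patients show 25%, the rate in all enrolled lies between 0.9 × 0.25 = 22.5% and 22.5% + 10% = 32.5%.

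**4. The tissue rule and responders.** The Discussion says neoadjuvant immunotherapy "enables approximately 30% of NSCLC patients to achieve major pathologic response (MPR) or even a pathological complete response (pCR". Take 30% as the responder share and let f (assumed) be the fraction of responders failing the rule. The share in the analysed cohort is 0.30(1 − f)/(1 − 0.30f):

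- f = 0.25: 0.225/0.925 = 24.3%
- f = 0.50: 0.150/0.850 = 17.6%
- f = 0.75: 0.075/0.775 = 9.7%
- f = 1: 0%

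The document gives no value for f.

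**5. Direction.** Assume 20% best, 70% middle and 10% worst responders, with two-year event rates of 10%, 30% and 80%. The rate in all is 0.02 + 0.21 + 0.08 = 31.0%. Without the best it is 0.29/0.80 = 36.3%; without the worst, 0.23/0.90 = 25.6%; without both, 30.0%. All these inputs are assumptions. They show only that the selections pull in opposite directions and can nearly cancel for DFS while the response range is still cut.

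**6. Can the planned adjustment help?** The matching and regression covariates are all measured at baseline. Residual tumour is measured after treatment and drives selection in one cohort only. Balance on baseline covariates does not restore patients removed for their response.

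**The case against.** The strongest reply on follow-up is that the criterion may be a screening rule, keeping out people whose records or follow-up could never be obtained. The loss limit, the imputation and the right to withdraw all suggest the authors regard lost patients as members. This stands as a plausible account of intent, but neither criterion says it and one is in the past tense, so the sections still conflict.

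On tissue, the Introduction says multi-region samples are taken after neoadjuvant therapy precisely to study how tumours regress. The sampling section allows extra sites for smaller tumours and sets no viable-tumour threshold. A reader might infer that many patients with major pathological response are removed and that only middling responders remain. The document does not support that: it does not say how much tissue such patients have or how many fail the rule. What remains is that some strong responders, complete responders above all, can fail it.

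A reader might also infer that the worst responders are improperly removed, through "2) Evidence of distant metastasis before surgery or inoperable state" and the definition of the neoadjuvant cohort by resection. A study of surgical tissue reasonably targets resected patients. That limits what the results apply to, and calls for a label rather than a charge of error.

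Finally, an article may leave analysis sets and patient flow to a fuller document, so their absence is not the complaint. The complaint concerns rules that this article states. A tissue study does need tissue, but that justifies an analysis-set rule, not exclusion from a cohort with DFS and OS as primary endpoints.

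**Conclusion.** The point holds on the wording. Eligibility is conditioned on facts that arise after consent. The follow-up criterion contradicts the sample-size and missing-data sections, and the two-region rule can under-represent strong responders in the neoadjuvant cohort in a way the planned adjustment cannot correct.

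The size and net direction of the bias are not derivable from the document. At the plan's own 25% event rate and 10% loss, the shift from dropping lost patients runs from +1.3 to −4.2 points for assumed rate ratios of 0.5 to 3. The 30% responder share is a ceiling on those at risk of exclusion; if half of them failed the tissue rule, an assumption, responders would fall to 17.6% of the analysed cohort. A reader might compute a larger overstatement of the neoadjuvant event rate by removing every responder at invented event rates, but that is the extreme case and not an estimate. The contradiction and the selection mechanism need none of these assumed values.

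**What to change.** 1. Delete follow-up availability from inclusion item 4 and exclusion item 5. Keep enrolled patients with confirmed NSCLC in the DFS and OS analyses, censored at last contact, and reconcile this with Missing data handling so that the 10% check counts them. Censoring assumes that loss is unrelated to outcome, so the planned completer comparison and sensitivity analyses remain necessary.
2. Apply tissue sufficiency and the two-region rule only to a tissue-evaluable set for the multi-region analyses. Keep resected neoadjuvant patients with little or no residual tumour in the DFS, OS and pathological-response analyses.
3. Report how many consented neoadjuvant patients do not reach resection. Label the neoadjuvant DFS and OS results, and the neoadjuvant versus naïve comparison, as conditional on resection.

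Retaining every consented person regardless would go too far. It would keep patients whose suspected tumour proves not to be NSCLC, and patients without surgery, who have no pathological response and no place in a blood schedule whose postoperative draws are anchored to surgery.

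**Cost.** An amendment to the eligibility wording and one analysis-set definition. Some patients will contribute clinical data without tumour omics. With 289 cases needed for modelling and 300 planned, the count of patients usable for the tumour-based model should be tracked separately from enrolment.
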